### Physical activity intervention

The physical activity intervention will comprise a weekly exercise session, taking place on the same day of the interactive session, and the use of pedometers to promote the increment of PA during the rest of the week. To progressively reach the 60 minutes of MVPA, we will aim that adolescents take 10000 to 11700 steps every day by the end of the intervention [53], specifying individual plans depending on their initial physical activity stage.

The exercise sessions will comprise several types of activities, from group classes focusing on aerobic exercises, sports, walking or running periods, dance, to strength sessions. We intend to show an extended array of activities that can be then adopted by the participant. Each session is planned for 60 minutes providing moderate to vigorous intensities.

More specifically, the strength sessions are planned according to the initial assessment carried out according to the 10-RM test. The training load is estimated for 50% of theoretical 1-RM [54]. The training plan consists of a circuit with 8 exercises for strength training, alternating between the torso and lower limbs. There will be 2/3 series of moderate intensity (30″ activity alternated with a 30″ break) or vigorous intensity (45″ of activity alternated with a 15″ break), thus respecting all of the recommendations [55]. Moderate to vigorous cardiovascular exercises, from 50 to 85% of the HR Reserve [54] will also be included, with a total volume of 10 to 30 minutes, according to the choice of the participants. The intensity of each exercise will be monitored both through the use of a heart rate monitor and the use of the perceived exertion scale for young people (OMNIA-RES) [56].

### Discontinuation

If participants miss more than 25% of the sessions, they will be removed from the analysis. The intervention will be discontinued if more than 50% of participants give up.

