## Abstract

**Background:**

Adolescent obesity epidemic is one of the major health priorities as it tracks into adult life. There is widespread need for new creative strategies and lifestyle programs. This study was designed to investigate the possible impact of including peers on the weight management program and assess the long-run adherence to behaviour change, with a potential positive impact on body mass index, body composition, and physical activity. Peer influence is major at this age and it is expected that adolescents will be better motivated and engaged in the behaviour changes when they are accompanied by their friends.

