## Methods/design

### Study design and setting

The study is experimental and will be based on a Non-Randomised, non-blinded Controlled Trial including two groups: a) A Comparison group, which will receive the standard treatment at the clinical setting, including medical assessment, dietary and PA counselling every 3 months, with access to a 12-month programme including weekly IS and PA sessions and holiday camps; b) An experimental group which, in addition to the standard treatment, will have access, together with a peer of their choice, to a 12-month programme including weekly IS and PA sessions and holiday camps. The adolescents will be allocated to the groups according to the existence or not of peers of their choice to escort them in the intervention.

The setting of the study will be an Exercise and Health University Study Centre and the Paediatric Obesity Outpatient Clinic at Hospital Santa Maria (HSM). All participants will be recruited in the Lisbon region, Portugal (Figure 1).

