### Subject withdrawal

The following will give rise to the withdrawal of participants:

•Attendance less than 75% of the IS or PA sessions;

•Acute illness implying non-compliance with the planned sessions;

To ensure that the participants comply with the assumptions, records will be kept of the attendance at the IS and PA sessions. Participants will not be substituted.

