### Interactive sessions

Both the comparison and experimental groups will meet the intervention team once a week. These meetings are conducted with both groups, with the intervention being identical in its contents, since the differential factor is the presence or absence of the peer of choice. The joined session will last for about 120 minutes, covering contents on PA/exercise, nutrition and behavioural change in a context of small activity groups (including peers), using an experiential learning methodology, which consists of increasing one’s skills through transforming the experience [35].

The main objective is to bring the participants closer to independent decision making on their wish to make changes about their lifestyle and weight status (and how to do so), and subsequently help them to face the consequences of their choices, regardless of the results.

The participants are encouraged to discover situations in their daily lives that can be changed in order to increase the number of calories burnt by more than 2000 Kcal per week [39]. This can be achieved more formally (physical exercise in a guided context) or informally (PA). The University offered an exercise room that is available for daily use by the participants. Each participant will be given a pedometer to help monitor the number of steps taken each day. The use of pedometers has been associated with significant increases in PA and significant reductions in BMI [40].

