### Data analysis

We plan to use repeated measures analysis of variance to evaluate the impact of the intervention. Additionally, we plan to use structural equation models and/or multiple mediation analyses to assess the presence of predictors of the results of the intervention [58].

The intention-to-treat principle (last observation carried forward) will be followed for handling the missing data.

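### Low attenders are removed from the analysis while intention-to-treat is claimed: the two rules conflict, and the removal selects on attendance recorded after allocation

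*Protocol article*

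**What the plan says.** Three sections of the protocol article bear on who is analysed.

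- **Discontinuation:** "If participants miss more than 25% of the sessions, they will be removed from the analysis". The sentence carries no condition and is not tied to a secondary analysis.
- **Subject withdrawal:** one listed cause of withdrawal is "Attendance less than 75% of the IS or PA sessions". The section adds "Participants will not be substituted".
- **Data analysis:** "The intention-to-treat principle (last observation carried forward) will be followed for handling the missing data".

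No section assigns the removal to a per-protocol or sensitivity set.

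On the role of the peer, the Abstract (Background) says "it is expected that adolescents will be better motivated and engaged in the behaviour changes when they are accompanied by their friends" and names as an aim to "assess the long-run adherence to behaviour change". Interactive sessions explains that the content is identical in both arms, "since the differential factor is the presence or absence of the peer of choice". Allocation is not random. Under Study design and setting: "The adolescents will be allocated to the groups according to the existence or not of peers of their choice".

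**The concern.** A reader cannot tell which set of adolescents produces the main result. If the Discontinuation rule governs, the analysis is a completer analysis under an intention-to-treat label. If the Data analysis rule governs, the removal sentence is wrong.

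Two things are at stake if removal is applied.

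- **Between arms.** Attendance is recorded during the programme, so it comes after allocation. The peer is the only intended difference between arms and is expected to raise motivation and engagement, so an effect on attendance is plausible. If the arms then lose different numbers or kinds of participants, the retained groups differ for reasons unrelated to any effect on the outcomes.
- **Within arms.** If adolescents who attend more also do better, the change reported in each arm exceeds what the programme achieves in all who were allocated. A study with an adherence aim would be leaving out its poor adherers.

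**Working it through.** **1. The rules side by side**

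| Section | Rule | Who is analysed |
|---|---|---|
| Discontinuation | missing more than 25% of sessions leads to removal | those attending at least 75% |
| Subject withdrawal | attending under 75% leads to withdrawal, no replacement | not stated |
| Data analysis | intention-to-treat, last observation carried forward | all allocated |

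The first and third rows name different sets. If carry-forward applies only to gaps among those retained, the intention-to-treat label is wrong. If it applies to everyone allocated, the removal sentence is wrong. Text must change either way.

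**2. The plan's own power figures**

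Inputs from Sample size calculations: two-sided 0.05, effect size 0.25, N = 134, power 0.90, falling to 0.82 at about 25% attrition. Data analysis names repeated measures ANOVA. The effect-size metric is not named; I take it as Cohen's f. I assume k = 2 measurements with correlation ρ = 0.5, as the article gives neither.

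Between-group test: noncentral F with 1 and N − 2 df, λ = f² × N × k / (1 + (k − 1)ρ).

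- N = 134: λ = 0.0625 × 134 × 2 / 1.5 = 11.17, power 0.913 (stated 0.90).
- 134 × 0.75 = 100.5. N = 100: λ = 8.33, power 0.816. N = 101: λ = 8.42, power 0.819 (stated 0.82).

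Other pairs also come close: k = 4, ρ = 0.7 gives 0.904 and 0.803; k = 6, ρ = 0.7 gives 0.913 and 0.816. The fall to 0.82 is therefore consistent with analysing only about 100 of 134. Carrying values forward for everyone allocated would keep 134. This fits the removal rule better than the intention-to-treat statement. It is corroboration only, and it shows no error in the power figures.

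**3. Illustrative size of the selection effect**

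Assumptions, none of them in the article: attendance propensity and outcome are jointly normal with correlation r; the peer has no true effect on the outcome; the peer alters only how many fall below the attendance cut. If a fraction p of an arm is retained from the top, the mean propensity of those retained is

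h(p) = φ(z)/p, with z = Φ⁻¹(1 − p),

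and the spurious contrast (experimental minus comparison, in SD of benefit) is r × [h(p_E) − h(p_C)].

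- h(0.80) = 0.2800/0.80 = 0.350
- h(0.70) = 0.3477/0.70 = 0.497
- h(0.60) = 0.3863/0.60 = 0.644
- h(0.90) = 0.1755/0.90 = 0.195
- h(0.50) = 0.3989/0.50 = 0.798

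Overall retention uses the planned arms of 99 and 35.

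| Removed, comparison / experimental | Retained overall | r = 0.2 | r = 0.3 | r = 0.5 |
|---|---|---|---|---|
| 30% / 20% | (79.2 + 24.5)/134 = 77.4% | −0.03 | −0.04 | −0.07 |
| 40% / 20% | (79.2 + 21.0)/134 = 74.8% | −0.06 | −0.09 | −0.15 |
| 50% / 10% (more extreme) | (89.1 + 17.5)/134 = 79.6% | −0.12 | −0.18 | −0.30 |
| 25% / 25% | 75% | 0 | 0 | 0 |

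The sign is negative, against the experimental arm, because in this model the comparison arm loses more of its low-propensity members.

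Within an arm, the retained mean exceeds the mean of all allocated by r × h(p). At p = 0.75, h = 0.3178/0.75 = 0.424, so the excess is 0.08 SD (r = 0.2) to 0.21 SD (r = 0.5).

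**4. Against sampling error**

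For a simple one-time contrast in SD units, the standard error is √(1/79.2 + 1/21) = 0.245 for the 40%/20% split and √(1/79.2 + 1/24.5) = 0.231 for the 30%/20% split. Over these two splits the bias is 0.029/0.231 = 0.13 to 0.147/0.245 = 0.60 standard errors.

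**The case against.** The conflict between the sections is hard to dispute, and an unseen analysis plan cannot make both statements true. The stronger case on the other side concerns what is built on the conflict, and much of it stands.

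- **A reader might infer that the set is selected on an outcome the peer is meant to change.** The article does not say this. Attendance is a process record in Table 1 and is absent from the outcomes in Table 2. The stated expectation concerns motivation and engagement in behaviour change, and nothing is said of session attendance as such. A peer effect on attendance is an inference.
- **A reader might infer that the rule necessarily deletes different kinds of adolescents from each arm.** That follows only if attendance or its determinants differ by arm, on which the article gives no data.
- **A reader might infer that removal would manufacture a peer benefit.** In the modelled mechanism the bias runs the other way. It would favour the experimental arm under another mechanism, for example if the peer lowered attendance, which the article does not suggest.
- **A reader might infer that the power allowance is breached.** It is not. The 40%/20% split removes (14 + 19.8)/134 = 25.2% and the 30%/20% split (10.5 + 19.8)/134 = 22.6%, both in line with the 25% planned.
- **Withdrawal need not mean that assessments stop.** Subject withdrawal does not say so, and the fix should not presume it.
- **The size is modest and rests on assumed inputs.** It is well under one standard error in the two main splits.
- **Intention-to-treat has no randomisation to protect here.** The arms may already differ, and analysing everyone does not cure that.

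None of this removes the contradiction or makes the completer set a sound primary set.

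**Conclusion.** The contradiction is certain on the text and must be resolved, because it decides who is in the main analysis. As written, the removal rule yields a per-protocol analysis selected on a post-allocation variable.

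The consequence is conditional. If attendance or its determinants differ by arm and are related to outcome, the between-arm contrast is biased. The illustrative size is 0.03 to 0.15 SD, for 30% or 40% removed in the comparison arm against 20% in the experimental arm and correlations of 0.2 to 0.5. This is neither a bound nor a prediction: a 50%/10% split gives 0.12 to 0.30 SD, and equal removal gives zero in this model. The article fixes neither the size nor the direction. That within-arm change looks too favourable depends on better attenders doing better.

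**What to change.** Reconcile Subject withdrawal, Discontinuation and Data analysis as follows.

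1. In Discontinuation, delete the clause that takes low attenders out of the analysis.
2. In Data analysis, state that the primary analysis includes every allocated adolescent in the allocated group, regardless of attendance.
3. In Subject withdrawal, state that the outcome assessments scheduled at 4 to 36 months are still sought after low attendance or withdrawal. Observed values then replace carried-forward ones where possible. Keeping everyone but relying on carry-forward over that span could exchange one bias for another.
4. Use the 75% rule only to define a labelled per-protocol sensitivity set, and say whether it counts each session type separately or both together.

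These changes concern data collection and analysis only. They take no position on who should continue in the programme.

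The cost is wording, effort to complete assessments that are already scheduled, and possibly smaller within-arm changes. The between-arm estimate could move either way. The change removes one selection step; confounding from allocation by peer availability remains and needs its own handling.

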### Data collection

The variables will be assessed according to Table 1.

**Table 1 T1:** Variables, measures and timing of the data collection

**Parameters**	**Assessed through…**	**When**
IS attendance	Attendance sheets	IS
Frequency of exercise	Training plans and attendance records	IS and Exercise sessions
PA	Pedometers (OMRON Walking Style II, HJ-113-E) PA records (7-Day Physical Activity Recall)	IS/Holiday Camps
PA and Sedentary behaviour	Accelerometers (Actigraph GT3X)	0, 4, 8, 12, 24, 36 months
BMI	Weight (OMRON BF-500) SECA height stadiometer	
% Fat mass	Bioimpedance (OMRON BF-500)	
Body composition	Dual-energy X-ray absorptiometry, DEXA (QDR-1500; Hologic, Waltham, MA)	
Physical fitness	FITNESSGRAM test battery	
Caloric intake	Food records (4-day recall)	
Quality of Life	Impact of Weight on Quality of Life – Kids (IWQOL-kids) Kidscreen-27	
Well-being	Rosenberg Self-Esteem Scale (RSES) Body Image Assessment Questionnaire (BIA) Body Shape Questionnaire (BSQ)	
Peers	Perceptions of Parents Scales (POPS) – adapted to peers Self-Perception Profile for Adolescents (SPPA) – Social Acceptance Scales and “Best Friends”	
Self-regulation variables	Treatment Self-Regulation Scale (TRS) Locus of Causality for Exercise (LCE) Weigh Management Self-efficacy (WMSE) Behavioural Regulation in Exercise Questionnaire (BREQ-2) The Psychological Need Satisfaction in Exercise Scale (PNSE)	

Notes: IS – Interactive sessions; PA – Physical Activity.

### Outcomes

Taking into account the recommendations of Barlow [57] and following analysis of the results of two recent meta-analyses [1,5], the following outcomes were defined (see Table 2).

**Table 2 T2:** Study outcomes

**Variables**	**Goal**
BMI	5% z-score reduction
Body composition	5% reduction of percent fat mass
Psychosocial	Improvements of 0.5 standard deviation
PA time	Increase moderate/vigorous PA (≥60 min per day)
Sedentary behaviour	≤ 90 minutes per day
Caloric intake	1000-1500 Kcal daily intake

Note: PA – Physical Activity.

### Data analysis

We plan to use repeated measures analysis of variance to evaluate the impact of the intervention. Additionally, we plan to use structural equation models and/or multiple mediation analyses to assess the presence of predictors of the results of the intervention [58].

The intention-to-treat principle (last observation carried forward) will be followed for handling the missing data.

## Discussion

The aetiology of paediatric obesity is influenced by biological, physiological, environmental and contextual factors [59], with human behaviour being the aggregator factor not only in obesity but in health in general [60]. This intervention is mainly intended for a better understanding of how behaviour can be modified.

Adolescence is that time in life where the ability to learn increases and new habits are adopted [61]. This issue is one of the strongest aspects of the intervention, which intends to enhance the perspective of positive health both based on the increasing individual autonomy and on the peer group interaction as a key element for understanding and potentiating various positive kinds of behaviours [62].

It is well known that only a small part of the populations undergoing interventions to lose weight actually succeed (and maintain) in the long term. Usually, as soon as the intervention ends, PA tends to decrease. As such, and as it is not possible to intervene directly in PA, where should we intervene? Research has shown how motivational processes may play a crucial role as mediators of behavioural change and maintenance [63]. Thøgersen-Ntoumani and Ntoumanis [64] showed the importance of encouraging self-determined motivation in order to improve the quality of the experience and the perpetuation of the behavioural change through exercise.

The sensation of choice or desire when facing a specific behaviour, places the individual in a privileged position in the motivation continuum [63], and can be manipulated through self-regulation. We believe this is a central question, given that SDT proposes that PA can be intrinsically motivated through increasing autonomy and skills development [63].

It is hoped that the results of this trial will contribute to increasing the knowledge on the different processes involved in the management of paediatric obesity (how, when, in which ways and why) and will enable to provide some answers that will for sure merit to be further explored.
